#### Ropeginterferon alfa-2b

The starting dose of ropeginterferon alfa-2b is 100µg every two weeks, which is increased as permitted in Table 3. In case of grade ≥ 3 AE suspected to be related to the study drug, ropeginterferon alfa-2b should be paused and restarted only after recovery to grade 1 or baseline values. Ropeginterferon alfa-2b should then be restarted at one dose level lower (i.e., reduced by 50µg). The lowest permissible dose is 100µg.

Ropeginterferon alfa-2b therapy should be discontinued if, during treatment: renal function decreases significantly; patients develop symptoms indicative of a thyroid dysfunction and thyroid stimulating hormone levels cannot be controlled within the normal range; newly diagnosed diabetes mellitus cannot be controlled by medicinal products; any increase in liver enzyme levels is progressive and clinically significant; hepatic decompensation develops; if psychiatric symptoms worsen; and/or any patient develops new or worsening eye disorders. Investigators should refer to the current summary of product characteristics for additional guidance on toxicity management.

### Concomitant medication

Appendix 6 contains a list of prohibited concomitant medications, and those to be used with caution during FEDORA.

### Treatment compliance

The local trial pharmacist is responsible for maintaining and updating the drug accountability logs in the Pharmacy File throughout the study which will be used to monitor compliance. Unfinished bottles and unused pre-filled pens from discontinuing patients will be returned to the trial pharmacist who will count and document any unused medication. All investigational medical products may then be destroyed in accordance with local procedures and documented on the drug accountability log in the hospital Pharmacy File.

Patients are issued with a Patient Diary to complete each day, recording the time that each dose was taken, and whether any doses were missed. The diary also includes a section where the patient can record any relevant information such as side effects suffered or reasons for missed doses. The completed diary will be collected by the centre at each protocol scheduled visit and checked. Relevant information should be recorded on the case report form (CRF). The completed diary should be retained with the medical notes as source data.

### Trial outcomes

The primary outcome is tolerability of combination therapy. A patient is classified as not tolerating treatment if they discontinue either fedratinib or ropeginterferon alfa-2b due to drug-related toxicity, due to delays in treatment exceeding 28 consecutive days due to drug-related toxicity, or if a treatment toxicity-related death is reported, within four months of starting combination therapy.

The secondary outcomes are:Tolerability of combination therapy throughout the treatment course. A patient is classified as not tolerating treatment as per the definition for the primary outcome.Best overall response (complete plus partial response) assessed using International Working Group criteria (spleen size measure by palpation) [30] within 12 and 24 months from starting combination treatment. Patients who die or do not have a disease response recorded prior to the relevant time points will be classified as non-responders.The highest tolerated dose of ropeginterferon alfa-2b, in combination with fedratinib, achieved by each patient. To be tolerated, the dose must have been maintained for at least one complete cycle.Toxicity, defined to be any grade ≥ 3 AE, or a SAE of any grade. See the Adverse Events Reporting and Analysis section for details.Overall survival, defined as the time from starting combination therapy to date of death from any cause. Patients who are alive at the time of analysis or lost to follow-up will be censored at their date last seen.Progression-free survival, defined as the time from starting combination therapy to first event or death from any cause. An event is defined to be any of the following: an increase in bone marrow fibrosis, an increase in spleen size by > 5cm, or transformation to acute myeloid leukaemia. Patients who are alive and event-free at the time of analysis or lost to follow-up will be censored at their date last seen.Quality of life assessed using the myelofibrosis symptom assessment form (MFSAF) v4.0 [31] total symptom score at trial entry, and three-monthly during treatment.Bone marrow fibrosis, assessed using consensus definitions [32] at trial entry and six-monthly during treatment.

The *JAK2*^V617F^ clone size, measured at trial entry and three-monthly during treatment, is an exploratory outcome.

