### Interventions

Table 2 provides an overview of a patient’s journey during the FEDORA trial.

**Table 2 Tab2:** FEDORA trial schedule of events

Assessment		Screening (within 60 days of registration)	Fedratinib pre-treatment Up to 3 cycles		Combination treatment					End of treatment visit^b^	
					Cycles 1–2		Cycle 3	Cycles 4 +	Follow-up on treatment		
			Day 1	Day 15	Day 1	Day 15	Day 1	Day 1	(Month indicated)^a^		
Informed consent		x									Follow up 3-mothly after treatment for survival, progression and subsequent treatment
Demographic data and medical history		x									
Clinical & physical assessment (Height^c^, weight, ECOG status, blood pressure, pulse, oxygen sats, respiratory rate, physical examination, fundoscopy^c^)		x	x	x	x	x	x	x		x	
ECG		x									
Pregnancy test^d^		x	x		x		x	x		x	
Laboratory Tests	Haematology^e^	x	x	x	x	x	x	x		x	
	Blast count/percentage^f^	x	x	x	x	x	x	x		x	
	Blood film assessment	x							6, 12, 18, 24		
	Biochemistry^g^	x	x	x	x	x	x	x		x	
	Coagulation^h^	x	x		x		x		6, 9, 12, 15, 18, 21, 24		
	Thiamine (vitamin B1) testing	x	After every 3 months of fedratinib treatment								
	Virology^i^	x									
	*JAK2*^V617F^ assessment^j^	x									
Spleen assessment	Palpation	x	x		x		x	x			
	Ultrasound	x							6, 12, 18, 24		
Bone marrow aspirate and trephine		x							6, 12, 18, 24		
Peripheral blood and serum samples for research, including *JAK2*^V617F^ clone size		x			D1 C2 only		x		6, 9, 12, 15, 18, 21, 24		
DIPSS score		x									
MFSAF		x							3, 6, 9, 12, 15, 18, 21, 24		
Disease response assessment (IWG criteria)									6, 12, 18, 24		
WHO bleeding score		x	x		x		x	x			
Fedratinib administration			Daily throughout the trial								
Ropeginterferon alfa-2b administration					Day 1 and 15 of each cycle, starting from Cycle 1						
Thiamine supplementation			Daily, alongside fedratinib treatment								
Transfusion assessment		x	Monitored continuously								
Concomitant medication			Monitored continuously								
Adverse events		x^k^	Monitored continuously								

*DIPSS* dynamic international prognostic scoring system, *ECG* echocardiogram, *ECOG* Eastern Cooperative Oncology Group, *IWG* internal working group, *MFSAF* myelofibrosis symptom assessment form, *WHO* World Health Organization

^a^Within 14 days of time-points indicated

^b^To be completed 28 days after last dose of protocolised drug

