### Statistical analysis plan

#### Sample size

The sample size for FEDORA is 30 patients. For the fedratinib plus ropeginterferon alfa-2b combination treatment to be considered acceptable, 80% of patients would need to tolerate treatment. If 60% or fewer patients tolerated treatment, then the combination would be considered unacceptable. Based on this, if there is a high probability that the true tolerability rate is greater than 70% then the treatment would warrant further investigation. Employing a conjugate beta-binomial analysis, with a minimally informative Beta(1,1) prior, if 23 of the 30 patients tolerate the treatment combination we would be 76% sure that the true tolerability is greater than 70%, and therefore warrant further investigation (Appendix 7).

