#### Outcome analysis

For the primary outcome, the total number and proportion of patients tolerating four months of treatment will be reported alongside the associated 95% credible interval, using the total number of patients who started combination therapy as the denominator (including patients who failed to find any tolerable dose). Bayesian posterior probability plots will be presented alongside the probability that the true tolerability rate is greater than 70%.

Analyses of the secondary and exploratory outcomes will be descriptive in nature, with no hypothesis testing conducted.The total number and proportion of patients tolerating up to two years of combination therapy will be reported alongside the associated 95% credible interval, using the total number of patients who started combination therapy as the denominator.Best overall response rate will be presented as the number and proportion of patients achieving a response, overall and by response category, over the total number of patients receiving combination treatment.The number and proportion of patients will be reported against the highest tolerated ropeginterferon alfa-2b dose that each individual patient received, having followed dose escalation schedule.Toxicity will be presented as the number and proportion of patients experiencing one or more grade ≥ 3 AEs, or a SAE of any grade. This outcome will be analysed using the safety population.Overall and progression-free survival will be presented using Kaplan–Meier plots. The median time to event and survival estimates at one year will be presented with 95% confidence intervals where appropriate.The MFSAF v4.0 analyses will be presented as medians with interquartile ranges over time. Multi-level models may be used to compare changes in scores from baseline to 12 months if appropriate.Bone marrow fibrosis will be tabulated and presented graphically, with number and proportion of patients at each level reported. In addition to this, individual patient results will be plotted to show change over time at the patient level.The *JAK2*^V617F^ mutant allele frequency will be presented as medians and interquartile ranges over time, overall and split by highest dose of ropeginterferon alfa-2b tolerated and summarised using descriptive statistics. Individual patient plots will also be presented showing raw percentages.

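### As worded, the best-overall-response rule turns a responder who later dies into a non-responder, and its time limit conflicts with the assessment window

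*Protocol article*

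**What the plan says.** The article's Trial outcomes section defines best overall response as complete plus partial response by International Working Group criteria, "within 12 and 24 months from starting combination treatment". The classification rule follows: "Patients who die or do not have a disease response recorded prior to the relevant time points will be classified as non-responders".

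Table 2 (Interventions) schedules the formal disease response assessment at months 6, 12, 18 and 24. Footnote a gives the visit tolerance: "Within 14 days of time-points indicated". It names no direction, so a visit may fall before or after the date.

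Under Outcome analysis, "Best overall response rate will be presented as the number and proportion of patients achieving a response, overall and by response category", with all patients receiving combination treatment as the denominator. The same section adds: "Analyses of the secondary and exploratory outcomes will be descriptive in nature, with no hypothesis testing conducted".

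The Discussion (Choice of trial design) names best overall response and progression-free survival as the secondary outcomes in which evidence of activity is sought.

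**The concern.** A best response over a period is settled once a qualifying response has been recorded; nothing later in the period can undo it. The rule as written does undo it. A patient with a complete response at month 6 who dies at month 11 becomes a non-responder at both time points. One who dies at month 20 becomes a non-responder at 24 months. The reported quantity is then response while still alive at the time point, which is a different measure from the one named and from the one the analysis section counts.

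The second problem is timing. The outcome covers responses within the period, but the rule accepts only those recorded before its end. For an assessment held at or just after month 12 or month 24, the two phrases give different answers, and these are the visits that close each period.

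At stake is one of the two outcomes offered as evidence of activity. With 30 patients, each reclassified responder moves the rate by 1/30 = 3.3 percentage points.

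**Working it through.** **The plan's own figures.** The article gives no target or expected value for best overall response, so there is nothing to reproduce for this outcome. Its one design probability concerns tolerability: "if 23 of the 30 patients tolerate the treatment combination we would be 76% sure that the true tolerability is greater than 70"%. With a Beta(1,1) prior, P(Beta(24, 8) > 0.70) = 0.755, which agrees with the stated 76%. It does not depend on the response rule.

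**What the death clause does.** Consider the four kinds of patient at a given time point.

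| Response recorded before the time point | Died before it | Rule as written | Best response within the period |
|---|---|---|---|
| No | No | Non-responder | Non-responder |
| No | Yes | Non-responder | Non-responder |
| Yes | No | Responder | Responder |
| Yes | Yes | **Non-responder** | **Responder** |

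A patient who dies without a response is already caught by the second condition. The death condition therefore changes the result only in the last row.

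**Size of the death clause (illustration).** Inputs:
- Median overall survival 6.5 years (Background; primary myelofibrosis only).
- First scheduled response assessment at month 6 (Table 2).
- 30 patients (Sample size).
- Assumed: constant hazard, counted from the start of combination therapy.
- Assumed: a third to a half of deaths after month 6 follow a recorded response. The article gives no response rate.

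Probability of death by t years = 1 − 0.5^(t/6.5):
- t = 0.5: 5.2%
- t = 1: 10.1%
- t = 2: 19.2%

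Only deaths after the first assessment can overturn a response recorded at a scheduled assessment:
- By 12 months: 10.1 − 5.2 = 4.9% (about 1.5 of 30 patients).
- By 24 months: 19.2 − 5.2 = 14.0% (about 4.2 of 30).

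Multiplying by one third and one half (unrounded percentages carried through):
- 12 months: 1.6 to 2.5 points, or 0.5 to 0.7 of a patient.
- 24 months: 4.7 to 7.0 points, or 1.4 to 2.1 patients.

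**Timing clause.** The window runs from day −14 to day +14, which is 29 days. Of these, 15 (52%) fall on or after the time point. If visits were spread evenly over the window (an assumption), about half of the month-12 and month-24 assessments would not be prior to their own time point. A first response read late at month 12 still counts towards the 24-month rate. A first response read late at month 24 counts nowhere.

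**The case against.** The strongest reply is that the sentence is a denominator rule: patients who die or lack a recorded response are kept in the analysis and counted as failures, not dropped as unevaluable. Such clauses are common, and nothing else in the article says that death revokes a response. This may well be the intent, and a reader should not infer that the investigators mean to strip responders of their status. But on that reading the mention of death adds nothing, and the sentence as it stands still classifies these patients as non-responders. Counting death as failure is also a legitimate composite, but it would then not be a best overall response.

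On timing, the objection carries more weight. *Prior to* may be loose for *by*. If a month means a 28-day cycle, as the equation of two years with 24 cycles might suggest, month 12 plus 14 days is day 336 + 14 = 350 and month 24 plus 14 days is day 672 + 14 = 686. Both precede the calendar anniversaries, and the conflict disappears. The article does not define the month for these visits, so the conflict stands as a matter of wording. A reader might go further and infer that the 12-month rate rests on the month-6 visit alone. That does not follow: the window also allows a month-12 visit before the date, and a response recorded then counts.

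A reader might also apply the one-third to one-half fraction to all deaths, giving about 3 to 5 points at 12 months and 6 to 10 at 24. That is too large, because no response assessment is scheduled for the patients who die before month 6.

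Finally, the outcome is descriptive with no target rate, the stated criterion for further investigation is tolerability above 70%, and deaths remain visible in the survival outcomes. All of this stands and limits the severity.

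**Conclusion.** The rule is wrong as written. Death before the time point overrides a recorded response, contrary to the outcome's own definition and to the analysis section. The timing wording is a second, weaker inconsistency, affecting only first responses read on or after the 12- or 24-month date.

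The illustrated understatement of about 1.6 to 2.5 points at 12 months and 4.7 to 7.0 points at 24 months is not a prediction. It rests on a survival figure for primary disease only, whereas the trial also enrols secondary myelofibrosis and selects on DIPSS risk, and on an assumed share of deaths that follow a response. If responders die less often than others, the effect is smaller.

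Severity is minor to moderate. The bias runs against the treatment, and the tolerability outcome and sample size are unaffected. A reader might infer that the phase III criterion is compromised, or that this is the main activity outcome. The documents support neither: the criterion is tolerability, and best overall response is named alongside progression-free survival. Nor is this a detail left to an unseen analysis plan, since the article itself states the rule.

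**What to change.** Replace the sentence in the protocol, and in the analysis plan if it repeats it, with:

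> Patients with no complete or partial response recorded up to and including the 12-month (24-month) assessment, with its 14-day window, are non-responders, including patients who die without a recorded response; a response recorded before death remains a response.

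This keeps deaths without response in the denominator as failures, preserves responses already achieved, and settles how the month-12 and month-24 visits count. If response while alive at the time point is truly wanted, it should be named as such and reported separately.

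The change is one sentence. It alters no visit, sample, data item or sample size, and should be made before the final analysis.

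### PFS is censored at last contact, yet no marrow or spleen examination is scheduled once treatment ends, so PFS may be overstated

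*Protocol article*

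**What the plan says.** Under Trial outcomes, the endpoint is "Progression-free survival, defined as the time from starting combination therapy to first event or death from any cause". The non-death events are "an increase in bone marrow fibrosis, an increase in spleen size by > 5cm, or transformation to acute myeloid leukaemia". The censoring rule is "Patients who are alive and event-free at the time of analysis or lost to follow-up will be censored at their date last seen", and overall survival uses the same censoring date.

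The same section lists "Bone marrow fibrosis, assessed using consensus definitions [32] at trial entry and six-monthly during treatment". In Table 2 (Interventions), marrow and spleen ultrasound fall at months 6, 12, 18 and 24 in the column headed "Follow-up on treatment". Palpation is marked at screening and on day 1 of treatment cycles. None of the three is marked at the end-of-treatment visit. After that the table has one entry: "Follow up 3-mothly after treatment for survival, progression and subsequent treatment".

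Under Outcome analysis, "Overall and progression-free survival will be presented using Kaplan–Meier plots", with a median and a one-year estimate. Under Interim and final analysis, patients who discontinue stay in the modified intention-to-treat population.

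**The concern.** Date last seen suits overall survival, because any contact shows that the patient is alive. It does not show that the marrow is unchanged or that the spleen has not grown. If a patient stops at month 5 for toxicity and is last contacted at month 24, the rule credits 19 months as progression-free, although no marrow or spleen examination was scheduled in that time.

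The exposed patients are those who stop for reasons other than progression, since progression on treatment is itself a reason to stop and would be recorded. Any missed progression pushes the PFS curve upward, and more so the more patients stop.

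The Discussion names best overall response and PFS as the evidence of activity. The two treat missing assessment in opposite ways: a patient with no recorded response counts as a non-responder, whereas unexamined time counts in favour of PFS.

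**Working it through.** **The plan's own figure.** The only design figure is for the primary outcome: with 23 of 30 tolerating and a Beta(1,1) prior, the posterior is Beta(24, 8), and P(rate > 0.70) = 0.755, which agrees with the stated 76%. The article gives no figure for PFS, so the check below uses assumed rates.

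**Inputs**
- Death rate: δ = ln 2 / 6.5 = 0.1066 per year, from the 6.5-year median survival in the Background.
- True one-year PFS: 75% (assumed). Total event rate λ = −ln 0.75 = 0.2877, so the progression rate is π = λ − δ = 0.1810.
- Share q stopping in year one for reasons other than progression: 20%, 30% or 40% (assumed). Stopping rate σ = −ln(1 − q) = 0.2231, 0.3567 or 0.5108. For scale, the 80% and 60% tolerability levels under Sample size imply 20% to 40% intolerant within four months, though some of these may stop only one drug.
- Share d of off-treatment progressions detected: 0 to 100% (assumed).

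Times are exponential, stopping is unrelated to progression, progression on treatment is seen when it occurs, and deaths always count.

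**Formulae.** With no off-treatment detection, the rule as written estimates

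S₀(t) = e^(−δt) × [σ + π e^(−(π+σ)t)] / (π + σ).

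With detection share d, it estimates d × S_true(t) + (1 − d) × S₀(t), so the excess shrinks in proportion to d.

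Example, q = 30%, t = 1: 0.8989 × (0.3567 + 0.1810 × 0.5841) / 0.5377 = 0.8989 × 0.8600 = 0.773.

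| Stopping in year one | One-year PFS, d = 0 | d = 50% | Two-year PFS, d = 0 | d = 50% |
|---|---|---|---|---|
| 20% | 76.5% | 75.7% | 60.7% | 58.5% |
| 30% | 77.3% | 76.1% | 62.9% | 59.6% |
| 40% | 78.1% | 76.6% | 65.0% | 60.6% |
| True value | 75.0% | 75.0% | 56.3% | 56.3% |

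At one year the excess is 1.5 to 3.1 points with no detection and 0.7 to 1.6 points with 50% detection. With full detection it is zero by construction.

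**The median.** Take a true one-year PFS of 65% (λ = 0.4308, π = 0.3241) and 30% stopping. The true median is 12 × ln 2 / 0.4308 = 19.3 months. Solving S₀(t) = 0.5 gives 26.2 months with no detection, and the same step with d = 50% gives 21.9 months. Two-year PFS with no detection is 52% against a true 42%.

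**Wider range.** A separate simulation treated every event as progression, with one-year PFS of 70% to 90% and 20% to 40% stopping. With no detection the excess was about 1 to 6 points at one year and 3.5 to 17 points at 24 months. With half detected it was about 0.5 to 3 and 2 to 9 points.

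**Check of the alternative rule** (75% scenario, true two-year PFS 56%, simulated):
- Everyone censored at the last assessment: 56% for all three stopping rates.
- Living patients censored at the last assessment but every later death counted: 53%, 51% and 49%. This understates PFS, because patients who stop remain in the risk set only if they go on to die.
- If the event rate doubles after stopping, censoring everyone at the last assessment also overstates PFS. With a one-year PFS of 80% on treatment and 40% stopping, the true one-year PFS is 76.4% and the estimate 80.0%.

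**The case against.** A reader might infer that progression is not assessed at all after treatment and that PFS is therefore overstated. The documents do not support that. Progression is a named purpose of the three-monthly follow-up, and Trial design says participants are followed monthly for two years without limiting this to time on treatment. The article does not say how progression is established off treatment, which is different from saying that it is not established. If all of it is detected, the excess is zero.

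The article also condenses a full protocol that is not shown and that may list the off-treatment examinations. That is a fair reason not to treat their absence as an error. It does not remove the point, because the article states outright both the censoring rule and the restriction of fibrosis assessment to the treatment period.

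The zero-detection figures are a worst case. They also hide transformation to leukaemia, which need not depend on a scheduled marrow or spleen examination. No two-year estimate is planned. At one year the excess is small beside the sampling error: with 30 patients and PFS of 75%, the half-width of an approximate 95% interval is 1.96 × √(0.75 × 0.25 / 30), about 15 points. All of this stands. Wide intervals do not excuse an error that runs in one direction, however, and the planned median is more sensitive than the one-year estimate.

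A reader might also infer that a poorly tolerated combination could look good enough on PFS to justify phase III. That goes too far. Further investigation is tied to the probability that tolerability exceeds 70%, early toxicity stops count against that outcome, and PFS is descriptive with no threshold.

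**Conclusion.** The concern holds as a risk of upward bias, not as an established overstatement. Followed as written, the plan can count time without the examinations that define two of the three non-death events as progression-free, and missed progression can only raise the estimate. With true one-year PFS of 75% and 20% to 40% stopping in year one, the excess at one year is about 1.5 to 3 points with no off-treatment detection, about half that with 50% detection, and none with full detection. Later parts of the curve and the median are more exposed.

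Apart from the death rate, every rate here is an assumption, since the article gives no PFS, stopping or detection rate. The primary tolerability analysis is unaffected. The point is worth correcting because PFS is named as evidence of activity and the rule is cheap to change before the final analysis.

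**What to change.** - Censor PFS at the last disease assessment able to show progression: a spleen examination or marrow, including any done in post-treatment follow-up.
- Keep date last seen for overall survival only.
- State that a death counts as a PFS event only if it falls within a set window after the last adequate assessment, and that otherwise the patient is censored at that assessment. Fix the window in advance, and make it long enough to span the gap between on-treatment assessments so that deaths on treatment still count. No particular length was simulated here.
- Report PFS under the date-last-seen rule as a sensitivity analysis.
- State how progression is established in the three-monthly follow-up. If the full protocol already says so, refer to it. The more examinations are done off treatment, the less the two rules differ.

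The cost is a few sentences in the protocol and analysis plan, shorter PFS follow-up and wider intervals. Some bias remains if stopping treatment is related to prognosis. Only continued assessment after stopping would address that, at the price of more visits and examinations.
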